### Sample size

At the study design stage, the funder advised that a minimum of 280 mainstream schools would be available to be randomised. Assuming an average of 925 students per school, an average base rate of 12.6 s.47 enquiries per 1000 students per school year under usual practice conditions, and a between-school coefficient of variation of 0.45 within LAs (these estimates are all based on comparator school data from the three pilot studies in Lambeth, Stockport and Southampton) [4], randomising 140 mainstream schools to each group provides 90% power to detect a decrease in rates from 12.6 to 10.48 per 1000 pupils per school year (i.e. a rate ratio of 83.2%). This is using a two-sided 5% type I error level when using a Poisson regression model accounting for cluster randomisation [8].

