#### Impact evaluation

The primary research question is: What is the impact of SWIS in reducing rates of Section 47 enquiries (across 2 academic years, starting on 2nd September 2020 and measured 23 months later), compared to usual practice? (***RQ1***) Secondary research questions are: What is the impact of SWIS on:

rates of referral to CSC and Section 17 assessments? (across 2 academic years, starting on 2nd September 2020 and measured 23 months later) (***RQ2***)the number of days children spend in care? (across 2 academic years, starting on 2nd September 2020 and measured 23 and 35 months later) (***RQ3***)educational attendance (recorded termly across 2 academic years, starting on 2^nd^ September 2020) (***RQ4***) and attainment (recorded June 2021 and 2022)? (***RQ5***)

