### Sequence generation

Mainstream schools were allocated to SWIS or usual practice in a 1:1 ratio whilst minimising covariate imbalance within and across blocks using a balancing algorithm for cluster randomised trials with multiple blocks [9], with LAs acting as blocks. This was implemented in R version 3.6.0 [10] using code provided as supplementary material to [9]. For the first block, the standard imbalance metric (Equation 1 in [9]) was used. The allocation of subsequent blocks was conditional on blocks already allocated, using a modified imbalance metric (Equation 2 in [9]). Balancing variables were school size (total number of students enrolled in year 7 and upward) and proportion of students eligible for free school meals (FSM). Both balancing variables were weighted equally, and will be adjusted for in the final statistical analysis. The rationale for selecting these variables is as follows:

**School size (total number of students enrolled).** The size of the school and number of students is likely to have an effect on how the social worker engages with and works within the school. In a larger school their time and resources may be spread across more students, and there may be more professionals to work with. It is reasonable to expect that this is a factor that will shape the implementation of SWIS and therefore balancing school size between groups is sensible.**Proportion of students eligible for free school meals.** FSM are provided for children resident in lower income households. They are designed to ensure that all children have access to adequate nutrition when they are at school. Eligibility for FSM is a reliable indicator that a child is from a low income household [11]. This is important because the work of CSC tends to be focussed on children from lower income households, and it is these children who are more likely to require a service from CSC [12].

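### The stated inputs give 80% power with 140 schools per arm, not 90%; the 23-month window raises this only to about 86%

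*Protocol article*

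**What the plan says.** The Sample size section gives a full set of inputs and one result.

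- Cluster size: "Assuming an average of 925 students per school".
- Control rate: "an average base rate of 12.6 s.47 enquiries per 1000 students per school year under usual practice conditions".
- Between-school variation: "a between-school coefficient of variation of 0.45 within LAs".
- Test: "This is using a two-sided 5% type I error level when using a Poisson regression model accounting for cluster randomisation".
- Result: "randomising 140 mainstream schools to each group provides 90% power to detect a decrease in rates from 12.6 to 10.48 per 1000 pupils", also expressed as a rate ratio of 83.2%.

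The section lists no allowance for loss of schools, no gain from covariates and no exposure other than the school year. Sequence generation confirms equal allocation. Under Objectives (Impact evaluation), the primary question now runs "across 2 academic years, starting on 2nd September 2020 and measured 23 months later". The Primary outcome section sets the same window, 2 September 2020 to 31 July 2022. The Sample size section does not say that it was recalculated when the trial was extended.

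**The concern.** A detectable effect, a number of clusters, a between-cluster coefficient of variation and a significance level together fix the power, so the printed 90% can be checked directly. It does not follow from the other printed figures. The gap is too large for rounding or for a choice between standard formulas.

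This is the headline design claim for the primary outcome. If the result is null, readers will set it against the stated power. They would believe that a true 17% reduction had a 10% chance of being missed, when on the stated basis the chance is 20%.

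**Working it through.** **Inputs** (all from Sample size unless noted)

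- λ0 = 0.0126 and λ1 = 0.01048 per pupil per school year
- k = 0.45
- c = 140 schools per arm
- y = 925 pupil-years per school for one school year
- two-sided 5%, so z = 1.960
- 23-month window (Impact evaluation): y = 925 × 23/12 = 1772.9, assuming that the annual rates and k are unchanged

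**Rate ratio.** 0.01048 / 0.0126 = 0.8317. The printed 83.2% reproduces.

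**Formula.** For an unmatched cluster trial comparing rates:

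c = 1 + (z_α/2 + z_β)² × V / (λ0 − λ1)², where V = (λ0 + λ1)/y + k²(λ0² + λ1²)

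**One school year, as stated**

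- Poisson part: 0.02308 / 925 = 2.495 × 10⁻⁵
- Between-school part: 0.2025 × (1.5876 + 1.0983) × 10⁻⁴ = 5.439 × 10⁻⁵
- V = 7.934 × 10⁻⁵
- (λ0 − λ1)² = 0.00212² = 4.494 × 10⁻⁶
- V / (λ0 − λ1)² = 17.653
- Schools per arm for 80% power: 1 + 7.849 × 17.653 = 139.6
- Schools per arm for 90% power: 1 + 10.507 × 17.653 = 186.5
- Power at 140: Φ(√(139 / 17.653) − 1.960) = Φ(0.846) = 80.1%

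**Log scale (the scale of a Poisson regression).** Variance of the log rate ratio = [1/(925 × 0.0126) + 1/(925 × 0.01048) + 2 × 0.2025] / 140 = (0.0858 + 0.1032 + 0.405) / 140 = 0.00424. Power = Φ(0.1842 / 0.0651 − 1.960) = 80.7%.

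**Simulation.** Gamma-Poisson counts, 20,000 runs, without covariates: 80.3% with a quasi-Poisson test and 80.6% with a robust standard error.

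**Reverse check.** Fix c = 140 and solve for λ1. At 80% power this gives 10.483 per 1000 (rate ratio 0.832), which is the printed detectable rate. At 90% power it gives 10.18 per 1000 (rate ratio 0.808).

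**Extended window**

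| Exposure | Power, rate scale | Power, log scale | Schools per arm for 90% | Rate ratio detectable at 90% |
|---|---|---|---|---|
| One school year | 80.1% | 80.7% | 186.5 | 0.808 |
| 23/12 years | 86.1% | 86.7% | 158.6 | 0.822 |
| 2 years | 86.4% | 87.0% | 157.3 | 0.822 |

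The simulation for 23 months gave 86.5% and 86.8%. The rate detectable at 90% power over 23 months is 12.6 × 0.8217 = 10.35 per 1000.

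**What would have to be true for 90%.** With 140 schools per arm and a rate of 10.48, k would have to be 0.36 for one year or 0.42 for 23 months. A one-sided 5% test over one year gives 87.7%, still short, and the section specifies a two-sided test.

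**The case against.** The arithmetic on the stated one-year basis is not in dispute. Five points can be made in the plan's favour.

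1. **Covariate adjustment.** The primary model adjusts for 2018/19 s.47 enquiries and free-school-meal eligibility. Over 23 months, 90% power needs k of about 0.416. That means covariates explaining 1 − (0.416/0.45)² ≈ 15% of the between-school variance within local authorities. If they explained 21% (k = 0.40), power would be 91.6%. The trial as now designed may therefore reach 90%. This stands as a possibility, but the protocol gives no figure for the explained share and the Sample size section does not claim the gain. On the stated one-year basis the share would have to be 1 − (0.358/0.45)² ≈ 37%.

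2. **Meaning of k.** If 0.45 were the raw variation of observed school rates, it would already contain Poisson noise. Removing it gives k² = 0.2025 − 1/(925 × 0.0126) = 0.1167, so k ≈ 0.34, and one-year power of about 91%. The section does not say so, and this reading leaves the match of 10.48 with the 80% solution unexplained.

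3. **Unseen method source.** The reference cited for the calculation is not at hand, so mislabelling is an inference. The shortfall does not depend on it, because the rate scale, the log scale and simulation agree.

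4. **The 23-month figure is conditional.** It assumes that rates and k stay the same across two pandemic years. The Primary outcome section also codes each pupil as having had an enquiry or not, so repeat enquiries may not accumulate and the gain could be smaller than shown. This stands, but it does not help the 90% claim.

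5. **Consequences are limited.** The number of schools was set by what the funder could offer, recruitment is complete, and the conclusion will rest on a rate ratio with its confidence interval. The estimate, its bias and the type I error are unaffected. This is correct: the error lies in the design claim and in how a null result will be read.

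**Conclusion.** The concern holds. With the inputs printed in the Sample size section, 140 schools per arm give 80% power (80.1% to 80.7%) for a fall from 12.6 to 10.48 per 1000, not 90%. The printed detectable rate is the 80% solution to two decimals, so a mislabelled power figure is the most likely cause. Over 23 months, power is about 86% to 87% for an unadjusted analysis with the annual rates and k = 0.45 unchanged. Reaching 90% requires an input that the section does not state, such as a covariate gain or a different definition of k.

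**What to change.** Correct the power sentence in Sample size and leave the number of schools as it is. Suggested content:

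- On a one-year basis, with k = 0.45 and a two-sided 5% test, 140 schools per arm give 80% power for a fall from 12.6 to 10.48 per 1000 (rate ratio 0.832).
- For the amended 23-month window, power is about 86% at a rate ratio of 0.832, or 90% at a rate ratio of about 0.82. State that this assumes unchanged annual rates and k and no covariate gain, and say how the once-per-pupil coding was handled.

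If the original calculation used an input that is not listed, such as an expected gain from baseline adjustment or a k defined on raw school rates, state that input and show that 90% follows from it.

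The cost is a short text change in the protocol and a less favourable power figure. Randomisation, data collection and analysis are not affected.

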### Recruitment

Participating LAs were chosen through a competitive tender process managed by the funder. Each chosen LA invited schools and gained the agreement from up to 16 schools to be put forward for randomisation. Recruitment of schools was completed for each LA before the list of schools was passed on to the trial statistician for randomisation. The statistician was not directly involved in the recruitment of schools. Schools were considered recruited once the LA confirmed that they have agreed to take part.

### Allocation to intervention or control groups

At the beginning of the study the research team received a list of up to 16 schools which had agreed to take part from each LA. The trial statistician performed the randomisation as described below, and the research team communicated the allocations to LAs via the funder.

### Sequence generation

Mainstream schools were allocated to SWIS or usual practice in a 1:1 ratio whilst minimising covariate imbalance within and across blocks using a balancing algorithm for cluster randomised trials with multiple blocks [9], with LAs acting as blocks. This was implemented in R version 3.6.0 [10] using code provided as supplementary material to [9]. For the first block, the standard imbalance metric (Equation 1 in [9]) was used. The allocation of subsequent blocks was conditional on blocks already allocated, using a modified imbalance metric (Equation 2 in [9]). Balancing variables were school size (total number of students enrolled in year 7 and upward) and proportion of students eligible for free school meals (FSM). Both balancing variables were weighted equally, and will be adjusted for in the final statistical analysis. The rationale for selecting these variables is as follows:

**School size (total number of students enrolled).** The size of the school and number of students is likely to have an effect on how the social worker engages with and works within the school. In a larger school their time and resources may be spread across more students, and there may be more professionals to work with. It is reasonable to expect that this is a factor that will shape the implementation of SWIS and therefore balancing school size between groups is sensible.**Proportion of students eligible for free school meals.** FSM are provided for children resident in lower income households. They are designed to ensure that all children have access to adequate nutrition when they are at school. Eligibility for FSM is a reliable indicator that a child is from a low income household [11]. This is important because the work of CSC tends to be focussed on children from lower income households, and it is these children who are more likely to require a service from CSC [12].

### Data collection

#### Plans for assessment and collection of outcomes

A proforma will be supplied to the LA, who will complete and return it to the research team at each data collection time point. This process will be trialled in January 2021 prior to quarterly data transfers thereafter. Data relating to the economic evaluation (e.g. salary costs, recruitment costs and some activity time data) will also be collected in this way. Other data items required for the economic evaluation will be collected directly from individual social workers through online surveys (e.g. activity time spent implementing the intervention).

Educational outcome data will be collected from the NPD and made available anonymised at an individual-level (identifiers will be stripped from the dataset) [7]. One application will be made to the NPD in early 2023 to request the required datasets. As per the current timescales for the trial, listed below, it will be possible to access KS4 attainment and attendance data for the trial cohort and report in January 2024.

Date            Milestone

July 2022                        Intervention endsJanuary 2023            Interim report: impact on CSC outcomes, IPE and economic analysisApril 2023            Key Stage 4 and Absence data releasedJuly 2023            Days in Care (35m) data collection endsJanuary 2024            Final report: impact on educational and days in care outcomes

Data for the IPE will be collected primarily through online surveys and interviews. Online surveys of social workers and school staff (five surveys, one at the end of each term, all school social workers and all head teachers in intervention group invited; n = 144 social workers and circa 100–200 school staff) to gather programme-level data on implementation and attitudes and to assess how SWIS is implemented in each school (RQ6 and 8). These will be short, taking no more than fifteen minutes to complete, and administered via Qualtrics online survey platform. Interviews will form part of purposive LA case studies (n = 9; one set of 3 in terms 1–3).

### Data management

The following management plans are in place for each type of data.

#### CSC data

Data sharing agreements will be set up between LAs (Data Controller) and Cardiff University to enable sharing of data related to CSC. Data fields will be included in this data sharing agreement, data will contain no identifiers except for a school ID and/or trial allocation. A data lead will be identified at each LA, and the trial data manager will liaise with each data lead to confirm required fields. Building on our learning from the pilot, each LA will pilot data transfer during the set-up phase to ensure the data can flow and is in the correct format. These checks will be detailed in the data management plan. Once any issues are addressed in this pilot, data will be shared quarterly up to the end of the intervention (July 2022). A final data extract will be requested Summer 2023 for the days in care outcomes. Data will be reported by school year group and by month and provided to the Cardiff team in a proforma developed and agreed during the pilot. Data will be aggregated, and no individual-level data will be sent. These data will be securely transferred to Cardiff University and checked by the data manager. All data will be stored on Cardiff University servers in restricted folders available only to those on the trial team who require access. This will be detailed in the delegation log.

#### LA cost data

As per the data sharing agreement with each LA, data on costs will be sent to Cardiff using the same proforma developed for the CSC outcomes. This will be checked and prepared for onward sharing to the economics team at the University of Oxford.

#### Education data

Education attainment and attendance data will be accessed via the NPD. LAs will confirm the school identifier to the Cardiff team (Unique Reference Number, URN) to enable NPD to identify pupils in those schools. Education data for those pupils will be made available to the study team via their Secure Research Service–a remote access data safe haven (hosted by the Office for National Statistics) as per their data sharing processes [13].

#### Data processing

Trial data management staff will liaise with LA data leads and monitor proforma submissions at the specified time points. Progress will be recorded in a tracking system and all submissions will be quality checked. Automatic electronic validation checks built into the proforma will ensure data entered by LA staff complies with the specified formatting. Strict data checks will also be completed upon receipt of data collection proformas. The data manager will conduct data cleaning at each time point to ensure there are no missing/duplicated data or any outliers. Data cleaning will be a regular process and data queries will be raised with LAs if any discrepancies are found. All data queries will be logged within the tracker, and an audit trail maintained recording any changes to the data. Upon completion of data checks, the data manager will add the data to the master dataset and log the process as complete in the tracker.

### Confidentiality and data security

Personal data will be transferred to Cardiff University for the IPE. Personal data (name and contact details) of social workers, school staff and children will be transferred to Cardiff University by LAs for those who have agreed for this information to be sent. Study information will be made available to IPE participants prior to participation. A risk assessment has been signed off to mitigate any potential risks regarding confidentiality and identification while processing these data, and personal data will be stored on secure university network servers, with access limited to members of the research team. No personal data will be processed by Cardiff University for the impact evaluation or economic workstream. All data will be stored in a secure manner and processed in accordance with data protection legislation (in accordance to GDPR and UK DPA 18) and Good Clinical Practice (GCP).

The elements and timing of data collection are shown in Fig 1 below.

**Fig 1 pone.0265354.g001:**
[figure not shown]
SPIRIT checklist.

### Statistical methods

#### Statistical methods for primary and secondary outcomes

All primary analyses will be ‘intention to treat’ i.e. schools will be analysed in the groups to which they were randomised, regardless of adherence to the intervention. Missing outcome data will not be replaced. For the primary outcome analysis, a quasi-Poisson regression model will be fitted with fixed effects for LAs and cluster robust standard errors reflecting the clustering structure (schools within LAs) to compare rates of s.47 enquiries at 23 months by arm, using the number of students per school as the exposure scaling variable, and s.47 enquiries for 2018/19 (baseline) and % eligible for FSM as fixed-effect covariates. Using a quasi-likelihood model accounts for possible over- or underdispersion i.e. variance in the data that is higher or lower than expected under the standard Poisson model. Allocation will be included in the model as a fixed effect, and the intervention effect (model coefficients transformed into rate ratios) will be presented as point estimate with two-sided 95% confidence interval (CI) and p-value. If the estimated rate is lower in the SWIS arm than in the comparator arm and the 95% CI around the estimated rate ratio excludes the null effect (rate ratio = 1), effectiveness of SWIS at the 5% level will be concluded.

Secondary outcomes will be analysed in a similar way as the primary outcome, by fitting regression models with cluster robust standard errors depending on the type of outcome: quasi-Poisson for rates (referrals to CSC, s.17 assessments) and linear for continuous variables (days in care, educational attendance and attainment). For the school-level variables (referrals to CSC, s.17 assessments, days in care) we will include the same fixed-effect covariates in the model as for the primary outcome (allocation, LA, baseline outcome from 2018/19, % eligible for FSM) and also use the number of students per school as the exposure scaling variable. For the student-level variables (educational attendance and attainment) we will additionally include gender and ethnicity as covariates, and the baseline outcomes used will be 2018/19 attendance (for attendance) and KS4 results (for attainment). The p-values generated from the secondary outcome analyses will be adjusted for multiplicity using Hochberg’s step-up procedure.

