## Materials and methods

### Trial design

The study is a pragmatic cluster randomised controlled trial with two arms (one intervention and one control group) and mainstream secondary schools as the unit of randomisation.

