### Study setting

The study will be conducted in mainstream secondary schools in England, across 21 LA areas.

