#### Other secondary analyses

A secondary analysis will use per-term (or per-month, if available) outcome data and include term (or month) as an additional covariate in the model to explore potential implementation effects and/or seasonality. Another secondary analysis will assess the hypothesised mediators of change outlined in logic model (S1 Appendix) at the 23-month follow-up by fitting an interaction term between allocation and category of implementation fidelity (a Gold, Silver, Bronze categorisation will be developed based on a re-analysis of pilot data and other insights from the IPE). Any other subgroup analyses (e.g. by age group) will be agreed with service user input. The p-values generated from these secondary and subgroup analyses will also be adjusted for multiplicity using Hochberg’s step-up procedure. We will fit a two-level mixed-effects model with random LA effects as an additional robustness analysis.

Missing outcome data will not be replaced in the primary analysis, but we will perform null imputation for missing covariates, where we will replace missing values with 0, and create a dummy indicator for the covariate coded 1 if the value was missing, and 0 otherwise, and include the dummy in the regression. If more than 5% of outcome data are missing, we will consider repeating the primary analysis after multiple imputation. To assess the impact of non-compliance (if present), we will exclude intervention arm schools that did not adopt the intervention at all and then repeat the primary analysis, and we will also perform a complier average causal effect (CACE) analysis. Statistical code and anonymised data can be provided upon reasonable request, in line with Centre for Trials Research policy.

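### The primary CI appears to rest on only 21 LA clusters and needs a small-sample variance with a t reference; separately, the random-LA robustness model has no school term

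*Protocol article*

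**What the plan says.** Under Trial design, the protocol article takes "mainstream secondary schools as the unit of randomisation". The study runs "across 21 LA areas" (Study setting). Allocation was 1:1 "with LAs acting as blocks" (Sequence generation), so each LA contributes schools to both arms. Each LA "gained the agreement from up to 16 schools to be put forward for randomisation" (Recruitment).

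The primary outcome is a single aggregated count per school (Primary outcome). The section Statistical methods for primary and secondary outcomes specifies a quasi-Poisson model with "fixed effects for LAs and cluster robust standard errors reflecting the clustering structure (schools within LAs"). Effectiveness is concluded if the estimated rate is lower with SWIS and the two-sided 95% CI for the rate ratio excludes 1. Attendance and attainment are analysed at student level, also with cluster robust standard errors.

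Other secondary analyses adds: "We will fit a two-level mixed-effects model with random LA effects as an additional robustness analysis". It does not state the outcomes, the distribution or any dispersion term for this model. The same section plans an analysis of per-term or per-month data.

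**The concern.** With one row per school, the only grouping that holds several rows is the LA, so the stated nesting points to a sandwich variance built from 21 clusters. With few clusters an uncorrected sandwich is biased downward, and a normal reference ignores the uncertainty in the variance estimate. Because the conclusion depends on whether the CI excludes 1, a CI that is too narrow raises the chance of a false claim of effectiveness.

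The robustness model raises a different issue. Its two levels are the rows and the LA. Whether the randomised unit is represented then depends on what the rows are and which likelihood is used. If it is not represented, the robustness analysis can look far more significant than the primary for a spurious reason, and so lend it false support.

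**Working it through.** **Plan's own figure.** For type I error the plan gives only the nominal two-sided 5%, so there is nothing to reproduce on this point. The Sample size section supplies inputs. (Its statement that "randomising 140 mainstream schools to each group provides 90% power" is a separate matter: a standard cluster-rate formula on its one-year inputs gives 80.1%. Nothing below depends on it.)

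**Inputs from the article.** 280 schools, 21 LAs (280/21 = 13.3 per LA, at most 16), 925 students per school, 12.6 enquiries per 1000 per year, between-school CV 0.45 within LAs, follow-up 23 months.

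**Inputs assumed.** Set A: 13–14 or 4–16 schools per LA, with or without a baseline covariate, 23 months, 4,000 null trials per scenario. Set B: 10–16 schools per LA, LA SD 0.3 on the log scale, school-size SD 300, lognormal school effects, baseline correlation 0 or about 0.7, two school years, 6,000 null trials per scenario. The Monte Carlo standard error near 5% is about 0.3 percentage points (√(0.05×0.95/6000) = 0.0028; with 4,000 trials, 0.0034).

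**Step 1: primary model, rejection rate at nominal 5%, no true effect in any LA**

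| Variance and reference | Set A | Set B |
|---|---|---|
| LA clusters, uncorrected, normal | 7.5–8.0% | 7.4–7.9% |
| LA clusters, G/(G−1), normal | 6.7–7.3% | 6.7–7.3% |
| LA clusters, full finite-sample correction, normal | – | 5.6–6.2% |
| LA clusters, G/(G−1), t(20) | 5.5–5.8% | 5.2–5.9% |
| LA clusters, full correction, t(20) | – | 4.2–4.7% |
| School level, uncorrected, normal | – | 6.5–6.6% |
| School level, N/(N−p) corrected | 4.9–5.7% | 5.2–5.5% |

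A third null simulation agrees: 7.1–7.9% for the first two rows and 5.8% for G/(G−1) with t(20).

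**Step 2: effect varying between LAs around a null average** (assumed SD 0.15 on the log scale). School-level standard errors reject 9–10% (11% in the third simulation). LA-level ones reject 5.0–7.9%, the low end with the full correction and t(20), the high end uncorrected with a normal reference.

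**Step 3: effect on CI width (log scale).** G/(G−1) = 21/20 = 1.05, and √1.05 = 1.025. The t(20) quantile is 2.086, and 2.086/1.960 = 1.064. Together 1.025 × 1.064 = 1.09. The full correction adds (N−1)/(N−p) with p = 24 (21 LA terms, allocation, baseline, FSM): √(1.05 × 279/256) × 1.064 = 1.14. The CI is therefore about 9–14% wider than the uncorrected normal one.

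**Step 4: robustness model on school counts.** Expected count per school = 0.0126 × 925 × 23/12 = 22.3. Dispersion = 1 + 22.3 × 0.45² = 5.5. A plain Poisson model with LA terms only takes it as 1, so its rejection rate is roughly 2[1 − Φ(1.96/√5.5)] = 2[1 − Φ(0.83)] ≈ 40%. Simulation gives 35–44% (Set A, LA effects only), 38–43% (random LA effect under Set B assumptions, 3,000 trials, LA variance held at its true value) and 37% (third simulation). With a dispersion parameter the random-LA model rejects about 7.5%. A Gaussian model on the log rate, approximated with LA fixed effects, rejects 4–5%.

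**Step 5: robustness model on pupil rows.** With m = 300 pupils per school (assumed) and no school term, the variance is understated by the design effect 1 + (m−1)·ICC.
- ICC 0.05: 1 + 299×0.05 = 15.95; 2[1 − Φ(1.96/3.99)] = 62%.
- ICC 0.15: 1 + 299×0.15 = 45.9; 2[1 − Φ(1.96/6.77)] = 77%.

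Per-term or per-month rows raise the same problem, because each school then supplies several correlated rows. No figure was calculated for that case.

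**The case against.** The case on the other side is strong and has shaped the conclusion.

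- **The clustering variable is inferred.** The article does not name it. LA is the natural reading, but school is not excluded.
- **LA clustering is not an error.** A reader might infer that because schools are randomised, clustering on LA is wrong. The documents do not support this. Schools nest in LAs and LAs are the randomisation blocks, so LA clusters contain all school-level correlation. The article also expects variable implementation (Discussion), which makes differing effects plausible, and there school-level standard errors do worse (Step 2).
- **7–8% is not the trial's type I error.** It requires a normal reference with no correction or only G/(G−1). The article states neither, and such detail may properly sit in an analysis plan that is not shown. Its absence is therefore not itself a fault.
- **School variation is not always omitted.** A reader might infer that the mixed model drops it entirely. With one row per school, schools are level 1 and their variation can sit in a residual or dispersion term. The article adopts quasi-likelihood for the primary model because of possible overdispersion, and it does not say that the mixed model is plain Poisson or that it extends to pupil outcomes.
- **The stated pupil-level analysis is not affected.** Cluster robust standard errors at either school or LA level cover within-school correlation.

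What the objection does not remove: 21 clusters is few, the CI is the decision rule, and the robustness model as described gives the randomised unit no place once rows are pupils or repeated periods.

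**Conclusion.** The point holds as two bounded recommendations. First, if the primary CI is clustered on 21 LAs, the choice of correction and reference distribution moves the type I error from about 7–8% to about 5–6% (G/(G−1) with t(20)), or to slightly below 5% with the full correction. These rates rest on the simulation assumptions above, and the advantage over school-level errors rests on an assumed between-LA effect SD of 0.15. CR2 itself was not simulated.

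Second, the robustness model can mislead badly, but only conditionally: about 35–44% false positives if it is plain Poisson on school counts, and 62–77% on pupil rows under the assumed ICC and school size. It is an additional analysis and cannot trigger the effectiveness conclusion, so the harm is false reassurance and not a false primary claim.

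**What to change.** 1. **Primary model.** Name LA as the clustering variable, keep it, and state a bias-reduced (CR2) variance with Satterthwaite degrees of freedom or a t(20) reference. The simpler corrections in Step 3 widen the CI by about 9–14% relative to an uncorrected normal one.
2. **Robustness model, pupil-level or per-term rows.** Add a school random effect nested in LA.
3. **Robustness model, school counts.** Use a negative binomial model, an observation-level random effect or a dispersion parameter. The first two imply a variance that grows with the square of the mean, as a constant between-school CV does. The dispersion parameter still left about 7.5% in simulation.

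The changes take a few sentences and some software options before analysis. They need no new data and do not alter the design.
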